# Proximal ROw carpectOmy versus four-corner Fusion (PROOF-trial) for osteoarthritis of the wrist: study protocol for multi-institutional double-blinded randomized controlled trial

**DOI:** 10.1186/s13063-023-07544-1

**Published:** 2023-08-07

**Keywords:** Arthrodesis, Arthroplasty, Osteoarthritis, Randomized controlled trial, Wrist injuries

## Abstract

**Background:**

Scapholunate advanced collapse (SLAC) and scaphoid non-union advanced collapse (SNAC) are common types of wrist osteoarthritis (OA). Non-operative treatment consists of pain medication, splinting, and avoiding activities that induce pain. However, in case a course of conservative treatment is unsuccessful, operative treatment is needed. The two most conventional operative approaches for SLAC/SNAC OA are four-corner arthrodesis (FCA) and proximal row carpectomy (PRC). Although FCA is the gold-standard operative technique and may lead to superior grip strength, the evident benefit of PRC is that it obviates any need for hardware removal and controlling for bony union. To date, no high-quality randomized controlled trial comparing FCA and PRC exists. As clinical outcomes seem comparable, a trial that assesses patient-reported outcomes, adverse events, and secondary operations may guide clinical decision making between these two procedures. Thus, the aim of this multi-institutional double-blind randomized controlled trial is to study whether PRC is non-inferior to FCA in treating SLAC/SNAC OA. We hypothesize that PRC is non-inferior to FCA with lower economic expanses.

**Methods:**

The trial is designed as a randomized, controlled, patient- and outcome-assessor blinded multicenter, two-armed 1:1 non-inferiority trial. Patients with SLAC/SNAC-induced wrist pain meeting trial inclusion criteria will undergo wrist arthroscopy to further assess eligibility. Each patient eligible for the trial will be randomly assigned to undergo either FCA or PRC. The primary endpoint of this study is the Patient Rated Wrist Evaluation (PRWE) at 1-year after FCA versus PRC. Secondary outcomes include Quick-Disabilities of the Arm, Shoulder and Hand, EQ-5D-5L, pain, grip strength, wrist active range of motion, radiographic evaluation, and adverse events. Trial design, methods, and statistical analysis plan will be presented here.

**Discussion:**

We present an RCT design comparing FCA vs PRC for SLAC/SNAC-induced OA. The results of this trial will assist in decision making when planning surgery for SLAC/SNAC.

**Trial registration:**

ClinicalTrials.gov NCT04260165. Registered February 7, 2020.

**Supplementary Information:**

The online version contains supplementary material available at 10.1186/s13063-023-07544-1.

## Administrative information

Note: The numbers in curly brackets in this protocol refer to SPIRIT checklist item numbers. The order of the items has been modified to group similar items (see http://www.equator-network.org/reporting-guidelines/spirit-2013-statement-defining-standard-protocol-items-for-clinical-trials/).

## Introduction

### Background and rationale {6a}

Osteoarthritis (OA) of the wrist is a common disorder and can lead to pain and substantial functional impairment. Most cases are due to traumatic sequelae, although atraumatic OA of the wrist may follow similar degenerative patterns. Scapholunate advanced collapse (SLAC) and scaphoid non-union advanced collapse (SNAC) are the most common examples of wrist OA seen in the clinical setting.

Much like long-standing non-union of the scaphoid, attenuation of the scapholunate ligament commonly leads to a secondary development of wrist OA. Both conditions lead to abnormal joint kinematics with a further development of dorsal intercalated segment instability (DISI) deformity and a rotatory subluxation of the scaphoid. These changes initiate degenerative arthritis at the radioscaphoid articulation, followed by carpal collapse and midcarpal arthritis [1]. A four-stage classification of the progressive pattern of wrist OA was first described by Watson et al. [2] The pattern is presented in the Supplement 1 [2–4].

Among active patients, the progression of SLAC and SNAC usually leads to substantial pain and restriction in the range of motion (ROM). Conservative treatment consists of pain medication, splinting, and avoiding painful activities. However, if symptoms worsen with disease progression, operative treatment is preferred [5].

Various operative approaches exist depending on OA stage, patient requirement level, and expert opinion. One of the most common approaches to either SLAC or SNAC I-III OA is four-corner fusion (FCA). This procedure includes scaphoid excision and fusion of the remaining proximal and distal carpal rows (capito-lunate-hamato-triquetral fusion). Another commonly used motion-preserving reconstruction to SLAC or SNAC I-II is proximal row carpectomy (PRC), which includes the excision of the scaphoid, lunate, and triquetrum, creating a neoarticulation between the capitate and lunate fossa of the radius.

Although several studies report the outcomes of PRC and FCA, there is a paucity of high-quality evidence that would support the use of one technique over another. Two RCTs exist comparing these techniques [6, 7]. However, these trials suffer from methodological shortcomings, such as lack of blinding, high risk of selection bias, and incomplete outcome reporting. Generally, studies show no significant difference in ROM, grip strength, pain, or patient-rated outcomes [6–8]. However, some study groups suggest that FCA may be superior in terms of grip strength, while PRC may be preferable in terms of ROM, postoperative complications, and secondary operations [9–12]. Some studies indicate that PRC is more cost-effective [13, 14], while Daar et al. [15] concluded that FCA with cannulated compression screws is the most cost-effective approach. A long-term study reported fewer arthritic changes after FCA versus PRC. However, there was no apparent correlation between radiographic OA and patient satisfaction [16].

The most recent meta-analysis comparing PRC and FCA from Kamir et al. (2020) used flexion/extension ROM, grip strength, and pain level as outcome measures. They found that PRC was statistically but not clinically significantly better than FCA in all outcome measures [17].

Wrist OA due SLAC- and SNAC-degenerative pattern remains a common disorder encountered by a wrist surgeon. To date, most surgeons will choose to manage patients with SLAC/SNAC OA with FCA over PRC. However, the use of PRC has gained popularity among clinicians due its simplicity and predictable results, without the need to remove hardware or control for bony union. We hypothesize that PRC is non-inferior to FCA with lower economic expanses. While superiority of either procedure may be insurmountable to present, a thorough assessment of important considerations, such as AEs, postoperative pain, ROM, and convalescence time, should be examined by means of a randomized controlled trial (RCT). Thus, we planned a study protocol for a multicenter, double-blinded, randomized controlled non-inferiority trial comparing PRC vs FCA for the treatment of SLAC/SNAC I-II OA of the wrist.

### Objectives {7}

This is a multicenter study comparing the outcomes of PRC and FCA for the treatment of SLAC/SNAC I-II wrist OA. We also include patients with non-reconstructible scaphoid non-union or static malalignment of carpal bones after SL disruption. The primary endpoint of this study is the Patient Rated Wrist Evaluation (PRWE) at 1-year after FCA versus PRC. The objectives are listed in Table 1. The study includes a cost-effectiveness analysis.

**Table 1 Tab1:** Study objectives

**Primary endpoint**
Patient-Rated Wrist Evaluation
**Secondary endpoints**
Quick-Disabilities of Arm, Shoulder, and Hand
Pain (visual analog scale)
Global improvement
EQ-5D-5L
Wrist active range of motion
Grip strength
Adverse events and major adverse events
Progress of arthritic changes
Time to union (FCA group)

### Trial design {8}

PROOF is a multicenter, prospective, patient- and outcome assessor-blinded, randomized, controlled two-armed 1:1 non-inferiority trial. The CONSORT diagram of the trial cohort is presented in Fig. 1.

**Fig. 1 Fig1:**
[figure not shown]
CONSORT diagram of the trial

## Methods: participants, interventions, and outcomes

### Study setting {9}

The trial will be conducted in four Finnish hospitals: the Helsinki, Tampere, and Turku university hospitals and Central Finland central hospital.

### Eligibility criteria {10}

We will assess the eligibility of all patients with SLAC/SNAC pattern wrist OA, chronic SL dissociation, and scaphoid non-union referred to the study hospitals. A 3-month course of conservative treatment will be initiated and patients not responding to non-operative treatment will be referred to a recruitment investigator (RI) and screened according to the inclusion and exclusion criteria. RI will confirm the clinical and radiological diagnosis and ensure that an adequate period of conservative treatment is completed without significant response. Patients with a prior attempt to reconstruct scaphoid non-union or SL ligament will be eligible for this trial. If the patient is eligible and agrees to participate, signed informed consent will be provided and baseline data will be collected (Table 2).

**Table 2 Tab2:** Trial eligibility criteria

Inclusion criteria	Exclusion criteria
1. Patient with: a) Irreducible carpal collapse due to chronic SL ligament injury, with normal joint cartilage, or b) Non-re-constructible scaphoid non-union with normal joint cartilage, or c) SLAC/SNAC I-II OA	1. Patient suitable for: a) SL-ligament reconstruction, or b) Scaphoid reconstruction
2. Pain persisting after 3 months of conservative treatment	2. Ulnocarpal, pancarpal, or advanced lunocapitate OA
3. Age 18–75 years	3. Age < 18 or > 75 years
4. ASA I-II	4. Inflammatory joint disease
5. Sufficient skills in spoken and written Finnish or Swedish	5. Heavy smoking (over 20 cigarettes/day)
	6. Disease or medication attributable to the fusion rate
	7. Alcohol or drug abuse
	8. Unstable psychiatric condition
	9. Symptoms are attributable to another wrist or upper limb condition
	10. Neurological condition affecting upper limb function
	11. Previous operation on the affected upper limb within 6 months

*ASA*, American Society of Anesthesiologists classification

The participant will then be scheduled for a diagnostic wrist arthroscopy prior to randomization and any study procedures to further confirm eligibility. The surgeon will confirm the radiological diagnosis, that the cartilage of the lunate fossa, proximal lunate, and capitate is preserved (Outerbridge 0–2, Table 3) [18] and that both procedures, FCA or PRC, would be indicated in the clinical scenario. If the surgeon deems that SL ligament or scaphoid reconstruction can be performed, the participant is excluded.

**Table 3 Tab3:** Modified Outerbridge classification. Evaluation of articular cartilage during arthroscopy [18]

Classification	Description
0	Normal articular cartilage
1	Softening of the articular cartilage
2	Fibrillation or superficial fissures of the cartilage
3	Deep fissuring of the cartilage without exposed bone
4	Exposed bone

### Who will take informed consent? {26a}

Patients with SLAC/SNAC OA referred to the study hospitals will be screened for eligibility by RIs. All RIs are consultant level hand surgeons. Patients eligible for this trial will receive written and verbal information. The RI will obtain consent from the participants and collect baseline data prior to randomization. Each patient will be informed that participation in the trial is voluntary and withdrawal is allowed at any time.

### Additional consent provisions for collection and use of participant data and biological specimens {26b}

This trial does not involve collecting biological specimens for storage.

## Interventions

### Explanation for the choice of comparators {6b}

FCA has been the gold standard for treatment of SLAC/SNAC II-III wrist OA. However, the use of PRC has gained popularity among clinicians in SLAC/SNAC I-II OA due its simplicity and predictable results. The evident benefit of PRC is that it obviates the need for hardware removal and control for bony union. However, PRC cannot be performed in stage III OA as the capitolunar surface is involved [19]. In this study, FCA will act as standard treatment and PRC as active control in stage I-II SLAC/SNAC wrist OA.

### Intervention description {11a}

A uniform anesthesia protocol will be used. Brachial plexus blockade is the method of choice with or without general anesthesia to provide good immediate postoperative pain management. Preoperative antibiotic prophylaxis will be used (cefuroxime 1.5 g or clindamycin 600 mg). Each physician performing surgery is a consultant level hand surgeon familiar with both operative techniques used in this study.

The patient will be placed in supine position. A pneumatic tourniquet will be applied. For arthroscopy, the wrist is placed in a traction tower with approximately 10 pounds used for traction to allow visualization. Standard 3–4, 6R, radial and ulnar midcarpal portals will be used. A systematic examination of articular cartilage and extrinsic and intrinsic ligaments will be performed to confirm patient eligibility.

A standard dorsal approach through the third extensor (extensor pollicis longus-, EPL-) compartment will be used for both procedures. The posterior interosseus nerve (PIN) lying in the fourth compartment will be denervated. A capsulotomy will be performed as described by Berger et al. [20]. After capsulotomy, PRC or FCA will be performed according to the randomization. Absorbable sutures will be used for the closure of joint capsule and extensor retinaculum. The EPL tendon will be left outside the extensor retinaculum. Skin will be closed with non-absorbable interrupted sutures. A soft dressing and a short arm splint will be applied.

### Proximal row carpectomy

The detailed surgical technique used for PRC is described by Stern et al. [21]. When removing the proximal carpal bones, care will be taken not to damage the lunate fossa and the proximal surfaces of the capitate and hamate. Capsular interposition or temporary fixation of the distal carpal row to the radius with K-wires will not be performed. However, radial styloidectomy may be performed according to the surgeon’s discretion.

### Four-corner arthrodesis

The scaphoid will be outright removed. The articular surfaces between the proximal row and distal carpal bones will be decorticated, and two to three cannulated compression screws will be used for fixation. In case of ulnar translation or dorsal intercalated segmental instability (DISI), the lunate will be re-aligned. The approach will be pragmatic to secure stable fixation in each case. Antegrade fixation of the luno-capitate space is not preferred to preserve the articular surface of the lunate. If adequate compression between these bones is not achievable using retrograde approach, an antegrade approach will be used. A cancellous bone autograft will be harvested from the removed scaphoid, the distal radius available through the same incision, or both.

### Rehabilitation

All participants will undergo an identical standardized postoperative rehabilitation for the first 12 postoperative weeks. The short arm splint applied in the operative theater and stitches will be removed 3 weeks postoperatively. Thereafter, the participants will perform active ROM exercises 3–5 times a day. A short arm removeable splint will be used until 6 weeks after the procedure. From 6 weeks onwards, the participants will perform active and passive ROM exercises and will be allowed to use the hand as tolerated. A physio- and/or occupational therapist specialized in treating hand surgery outpatients will instruct the participants at 3 and 6 weeks after the operation. After 12 weeks, any other rehabilitation input beyond the protocol will be at the discretion of the RIs.

Patient rehabilitation will be followed by RIs at an outpatient clinic. Both the patient and RI will be blinded to the allocation until 12 months post-surgery. Outcome measures collected during follow-up are presented in the “Outcomes {12}” section.

Cone beam computed tomography (CBCT) will be performed alongside the clinical follow-up at 6 and 12 weeks and 6 and 12 months after study procedure. To maintain blinding, the CBCT will be screened by the surgeon who will give permission to continue according to the rehabilitation program if no adverse events occur that would compromise the rehabilitation program. Neither RIs nor patients will have access to CBCT imagining before the primary endpoint of the study has been reached at 12 months. Long-term follow-up will include standard PA and lateral X-rays at 5 and 10 years after the surgery.

### Criteria for discontinuing or modifying allocated interventions {11b}

Crossover will not be possible due to the nature of the study procedures. Both interventions will be pragmatic to fit the needs of each participant. For instance, the surgeons will be allowed to perform radial styloidectomy during PRC if deemed necessary (radial styloid impingement). However, temporary fixation of the distal carpal row to the radius with K-wires will not be performed as this would necessitate wire removal and compromise the allocation. The diameter and length of the cannulated screws, insertion site, and screw direction will be left to the surgeons’ discretion. Nonetheless, a stable fixation is mandatory to allow early ROM exercises and further ensure the concealment during follow-up. If stable fixation is not reached, the patient will be excluded and the surgery and the rehabilitation will be performed according to the judgment of the treating surgeon.

If any concerns about patient safety arise in clinical examination or radiological evaluation during follow-up, the concealment will be unveiled, and the patient treated according to the standard of care.

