### Concealment mechanism {16b}

The randomization will be performed by the research nurse by opening a sequentially numbered sealed opaque envelope after the surgeon has performed the wrist arthroscopy and confirmed the eligibility of the patient. As the envelopes will be kept in a secure, lockable cabinet that is only accessible by the study nurse located in the Helsinki University Hospital, an operating room nurse at each center will telephone the study nurse to receive and pass the knowledge of the allocation to the surgeon.

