## Statistical methods

### Statistical methods for primary and secondary outcomes {20a}

Statistical analysis will be performed with both per-protocol and intention-to-treat (ITT) methods, the latter being the primary analysis. Descriptive statistics will be presented as mean (standard deviation) or median (interquartile range) for continuous variables and count (percent) for categorical variables.

For the continuous outcomes, we will compare the groups using a mixed model for repeated measurements (MMRM) entering group, group*time interaction as fixed factors, study site as a random factor, and baseline value as a covariate to the model. Marginal effects with 95% confidence intervals from the model will be reported as treatment effects. For the global improvement, we will use ordinal logistic model.

Statistical significance is set at 0.05. As comparisons of secondary outcomes are considered hypothesis generating, we will not adjust for multiple comparisons.

A statistical software program will be used for analyzing entered data. Blinded data interpretation will be used to reduce interpretation bias; therefore, the biostatistician will be unaware of the group assignments when performing the analyses.

The criterion for statistical significance will be set at *p* = 0.025 (one-sided) or *p* = 0.05 (two-sided). All *p*-values will be reported to three decimal places, with those less than 0.001 reported as *p* < 0.001.

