### Methods in analysis to handle protocol non-adherence and any statistical methods to handle missing data {20c}

We will document the number and proportion of patients eligible for and compliant with each follow-up. If the number of patients withdrawing from either arm of the trial is greater than the anticipated 10% at 12 months, an analysis of the demographic and prognostic characteristics will be performed between the individuals who withdraw and those who remain in the trial. Moreover, data may not be available due to voluntary withdrawal of patients, lack of completion of individual data items, or general loss to follow-up. For reliable ITT analyses, we will collect 1-year outcomes from all participants despite possible protocol compliance fluctuation. Where possible, the reasons for missing data will be ascertained and reported. However, the main analysis will be performed using the available (not imputed) data.

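### As written, an FCA patient whose fixation is not stable is excluded after randomisation, which conflicts with ITT as the primary analysis and can affect one arm only

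*Protocol article*

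**What the plan says.** **Order of events.** Under Concealment mechanism {16b}, the envelope is opened "after the surgeon has performed the wrist arthroscopy and confirmed the eligibility of the patient". Under Intervention description {11a}, "After capsulotomy, PRC or FCA will be performed according to the randomization". Allocation is therefore fixed before any fixation is attempted.

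**Where fixation occurs.** In the Four-corner arthrodesis section, "two to three cannulated compression screws will be used for fixation". The Proximal row carpectomy section rules out temporary K-wire fixation and describes no other kind.

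**The rule.** Criteria for discontinuing or modifying allocated interventions {11b} calls stable fixation mandatory, so that early motion exercises and concealment are possible. It continues: "If stable fixation is not reached, the patient will be excluded", after which "the surgery and the rehabilitation will be performed according to the judgment of the treating surgeon".

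**The analysis.** Statistical methods {20a}: "Statistical analysis will be performed with both per-protocol and intention-to-treat (ITT) methods, the latter being the primary analysis". The section on non-adherence and missing data {20c} says that, for reliable ITT analyses, "we will collect 1-year outcomes from all participants despite possible protocol compliance fluctuation". It adds that the main analysis uses observed data without imputation.

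**The concern.** Whether fixation is stable can be known only during an FCA. The rule therefore acts after randomisation, on a result of the allocated operation, and has no counterpart in the PRC arm. A patient removed in this way should still count under ITT, yet nothing in {11b} says that follow-up or analysis continues.

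Two things are at stake. The first is the primary contrast. If patients with failed fixation have worse 12-month PRWE, dropping them lowers (improves) the FCA mean, and PRC is compared with a favourably selected arm. Because the main analysis uses observed data only, a patient without follow-up contributes nothing at 12 months and nothing stands in for that outcome. The second is the adverse-event and cost-utility comparison, from which intra-operative fixation failures may also drop out. Avoiding hardware removal and the need to monitor union is the article's stated advantage of PRC, so implant-related problems in FCA belong in that comparison.

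**Working it through.** **1. Can the rule reach both arms?** Randomisation follows arthroscopy {16b, 16c}, and the allocated procedure follows randomisation {11a}. Screws are used in FCA, and the PRC description contains no fixation. The rule can apply to FCA only.

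**2. What does 'excluded' mean?** Under Eligibility criteria {10}, the same word means removal from the trial, when arthroscopy shows that a reconstruction is possible; that removal comes before randomisation. Where the protocol intends patients to be retained, it says so: under {18b}, early unblinding is stated to leave follow-up and analyses unaffected. No such sentence accompanies the fixation rule.

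**3. Inputs from Sample size {14}.** Margin 11.5, SD 14, one-sided 2.5%, power 90%, 37 per group, 10% loss, 84 recruited. The recruitment step reproduces: 37/0.90 = 41.1, so 42 per arm, 84 in total. The 37 itself does not follow from the stated inputs: 2 × (14 × (1.960 + 1.282)/11.5)² = 31.1, so 32 per group, or 33 with the t distribution. That errs on the large side and is a separate matter; 37 is used below as stated.

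**4. Tolerated observed difference.**
- SE = 14 × √(2/37) = 3.25
- 95% half-width (t, 72 df) = 6.49
- 11.5 − 6.49 = 5.01 points

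Non-inferiority is shown only if the observed PRC minus FCA difference is below about 5.0.

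**5. Shift from exclusion.** Full FCA mean = retained mean + p × d, where p is the share excluded and d is how much worse the excluded are than the retained. The shift is p × d. The article gives neither quantity, so both are assumed. Power is for truly equal arms under full ITT, by two-sample t-test with 37 PRC patients and the FCA number shown; with nobody excluded it is 93.6%.

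| Assumed p | FCA analysed | Shift at d = 10 / 20 / 30 | Share of margin | Power at d = 10 / 20 / 30 |
|---|---|---|---|---|
| 2% | 36 | 0.2 / 0.4 / 0.6 | 2% / 3% / 5% | 92.5% / 91.6% / 90.7% |
| 5% | 35 | 0.5 / 1.0 / 1.5 | 4% / 9% / 13% | 90.8% / 88.0% / 84.8% |
| 10% | 33 | 1.0 / 2.0 / 3.0 | 9% / 17% / 26% | 87.0% / 79.8% / 70.5% |

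**6. Selection or lost numbers?** If the exclusions were uninformative (d = 0), power would be 93.3%, 93.0% and 92.3% at 2%, 5% and 10%. Nearly all the damage comes from selection.

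**The case against.** The strongest reply is that loss from ITT is inferred. The rule stands in a section on modifying interventions, its stated reasons are early motion and concealment, and its consequence concerns surgery and rehabilitation. It does not say that follow-up stops, while {20a} and {20c} point towards retention. Analysis-set definitions may also be in an analysis plan that is not shown. This stands to the extent that the milder reading is possible. But it is not stated, and the plain wording is the one used elsewhere for removal from the trial. An analysis plan also cannot recover outcomes that were never collected.

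It is also fair that the event may be rare. The surgeons are consultants familiar with both techniques, and the FCA section allows an alternative approach when compression is inadequate. Of 42 FCA patients, 2% is fewer than one and 5% about two. No rate is given, so this gives no firm assurance either way.

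Four stronger readings are not supported:

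- *The rule contradicts the statement "Crossover will not be possible due to the nature of the study procedures".* It leaves the surgery to the surgeon's judgment but names no conversion to PRC, and some other procedure would not be crossover to the other arm.
- *FCA failures vanish from the trial.* Only intra-operative failure to reach stable fixation is covered. Later non-union, implant complications and re-operations are still recorded under Adverse events and Radiological evaluation.
- *The rule uses up the 10% loss allowance.* Uninformative loss of 10% of FCA patients costs about one percentage point of power (93.6% to 92.3%).
- *The per-protocol result should become a second condition for success.* The protocol names ITT as primary, and this defect gives no reason to add one.

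**Conclusion.** The point holds. The fixation rule, as written, removes randomised patients from one arm on an intra-operative result, and it cannot be reconciled with {20a} and {20c} without further words. At best it can be applied in two ways that give different primary analysis sets.

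The size is unknown. Over the assumed range (2% to 10% excluded, 10 to 30 points worse) the shift is 0.2 to 3.0 points against a tolerated difference of about 5.0. That runs from negligible to enough to change the conclusion. The calculation uses SD 14, 37 per arm and an unadjusted comparison, whereas the planned model also adjusts for baseline.

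A reader might infer that the rule makes a false claim of non-inferiority more likely. If the excluded patients do worse, the opposite is true: the bias runs against PRC and can wrongly deny non-inferiority. That direction is plausible, but the article gives no data on it.

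**What to change.** Reconcile {11b}, {20a} and {20c} with wording to this effect: a patient in whom stable fixation is not reached leaves the protocol procedure and rehabilitation, with care at the surgeon's judgment as now. The patient stays in follow-up, has the 12-month PRWE, adverse events and costs collected, and is analysed in the FCA arm under ITT. Such patients are omitted only from the per-protocol set. The clinical rule itself is untouched.

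For any patient already excluded under the rule, retrieve the 12-month data where consent allows, and report how many there were.

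The cost is a protocol amendment, which under {25} goes through the steering committee, the Ethics Committee and the registry, plus follow-up of a few more patients. No extra recruitment is needed. Randomisation began in October 2020, so delay risks 12-month outcomes that cannot be recovered.
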